## Abstract

**Background:**

This observational study aims to establish the feasibility of using x-ray images of radio-opaque chemoembolisation deposits in patients as a method for real-time image-guided radiation therapy of hepatocellular carcinoma.

**Methods:**

This study will recruit 50 hepatocellular carcinoma patients who have had or will have stereotactic ablative radiation therapy and have had transarterial chemoembolisation with a radio-opaque agent. X-ray and computed tomography images of the patients will be analysed retrospectively. Additionally, a deep learning method for real-time motion tracking will be developed. We hypothesise that: (i) deep learning software can be developed that will successfully track the contrast agent mass on two thirds of cone beam computed tomography (CBCT) projection and intra-treatment images (ii), the mean and standard deviation (mm) difference in the location of the mass between ground truth and deep learning detection are ≤ 2 mm and ≤ 3 mm respectively and (iii) statistical modelling of study data will predict tracking success in 85% of trial participants.

**Discussion:**

Developing a real-time tracking method will enable increased targeting accuracy, without the need for additional invasive procedures to implant fiducial markers.

**Trial registration:**

Registered to ClinicalTrials.gov (NCT05169177) 12th October 2021.

## Background

Liver cancer is a global health concern with increasing incidence worldwide [1–3]. It is the sixth most common cancer globally and the third leading cause of cancer-related deaths [1]. Hepatocellular carcinoma (HCC) is the most common form of primary liver cancer accounting for ~ 85% of cases [1]. In Australia, the incidence and mortality rate of liver cancer has increased more than any other cancer [4].

Stereotactic Ablative Radiation Therapy (SABR) is a technique used to deliver high-precision, ablative doses of radiation in a small number of fractions to an extra-cranial target [5]. It is utilised to treat a variety of malignancies including in the lung [6], liver [7] and spine [8].

One of the challenges of radiation therapy (RT) is the significant movement of tumours that can occur during treatment, particularly for tumours in the liver due to respiratory motion [9]. SABR is often utilised as an alternative to surgery or thermal ablation in patients with limited functional liver reserve or where tumours lie close to bowel, pericardium, or central biliary structures. If respiratory motion is not accounted for, there can be increased dose to surrounding structures and subsequent injury. Therefore, the delivery of a precise ablative dose is highly dependent on being able to verify the tumour position and any associated movement [10]. Real-time image-guided radiation therapy (IGRT) is a targeting method used to track the movement of tumour tissue during radiation therapy by tracking the motion of fiducial markers implanted in or near the tumour tissue [11]. One of these technologies, Kilovoltage Intrafraction Monitoring (KIM), has recently been applied to liver SABR [12]. The markers are implanted by an invasive procedure which can be associated with a risk of bleeding, infection, marker migration, additional treatment delays and may require a general anaesthetic [13, 14]. The current study seeks to develop and investigate a deep learning method that maintains the real-time tracking benefits of KIM, without the need to implant markers into patients.

In HCC patients, chemotherapy is often delivered via transarterial chemoemobilisation (TACE), which involves the injection of chemotherapy drugs into the artery supplying the tumour combined with embolic particles to restrict blood supply and retain the therapeutic agent within the treatment zone, and a radio-opaque contrast agent. Radio-opaque contrast material within the tumour allows direct visualisation of the treated tumour at the time of TACE and is often retained in the tumour and visible on imaging for many months afterwards. The approach of treating HCC using TACE immediately before SABR is increasingly used, and there is the potential to utilise this retained radio-opaque contrast as a marker for non-invasive, real-time tracking of tumour motion [15–17].

The most common radio-opaque agent used in this setting is ethiodised oil, however, there are also some drug-eluting bead (DEB-TACE) formulations that incorporate iodine directly into the bead structure. These retained radio-opaque contrast agents are currently often used as a surrogate tumour marker to aid target verification before and during SABR.

This observational study aims to establish the feasibility of using residual radio-opaque contrast agent in patient images as a real-time guidance method for IGRT treatment of HCC by applying deep-learning to x-ray images obtained as standard of care during radiation therapy. Completion of this observational study will lead to a prospective use of real-time markerless KIM real-time IGRT for eligible liver SABR patients.

## Methods/design

### Aim

This study aims to provide a non-invasive alternative to implanting fiducial markers to track tumour movement in real-time during SABR treatment of HCC. To determine whether radio-opaque contrast agents in the radiological images used to guide HCC radiotherapy can be used for real-time tracking of tumour movement, this study will train a deep-learning model to segment residual radio-opaque agents in radiation therapy planning images then attempt to accurately detect the agents in images obtained during treatment, for use with motion management software (KIM). The deep learning real-time tracking process is shown in Fig. 1.

**Fig. 1 Fig1:**
[figure not shown]
The clinical workflow for automatic target tracking using residual contrast agent is comprised of two key components: prior to treatment and during treatment. A patient-specific network is trained prior to the patient’s treatment using radiation therapy planning data. The generator network from the conditional generative adversarial network (cGAN) is used during the treatment to segment the target. The location of the segmented target can be used for motion management

### Design

This observational study will recruit patients who had or will have SABR treatment for HCC following TACE chemotherapy. Standard of care radiotherapy planning and in-treatment x-ray images will be collected, and analysis will occur offline. Following deep-learning and KIM algorithm adaptation, the detected location of the contrast agent mass by KIM will be compared with manual delineation (Fig. 2).

**Fig. 2 Fig2:**
[figure not shown]
Study Design. Standardly collected radiation therapy planning, CBCT projections and intra-treatment monitoring images will be used to created manually delineated matches. After improvement of existing mass-detecting software (KIM) through machine learning, the updated algorithm will be applied to un-delineated images to (i) detect the contrast mass, and (ii) locate its centre in comparison with manually delineated matches. If the contrast mass can be detected accurately, modelling for likelihood of KIM tracking success will be conducted

### Hypotheses

We hypothesise that: (i) deep learning software can be developed that will successfully track the contrast agent mass on two thirds of cone beam computed tomography (CBCT) projection and intra-treatment images (ii), the mean and standard deviation (mm) difference in the location of the mass between ground truth and deep learning detection are ≤ 2 mm and ≤ 3 mm respectively and (iii) statistical modelling of study data will predict tracking success in 85% of trial participants.

### Eligibility criteria

This study will recruit 50 participants who: will be ≥ 18 years of age; had or will have SABR for HCC; will/have residual radio-opaque contrast (e.g., ethiodised oil or drug-eluting beads containing iodine) from prior TACE chemotherapy visible within the imaging field on RT planning CT scans; will provide written informed consent or meet criteria for a waiver of consent; and will have the minimum image dataset available in the required format.

### Participants

Participants will be recruited from four Australian sites that currently use SABR to treat primary liver cancer; Princess Alexandra Hospital in Queensland, Calvary Mater Newcastle Hospital and the Crown Princess Mary Cancer Centre in New South Wales, and the Austin Health in Victoria. The Image-X Institute at the University of Sydney will develop the KIM algorithm and software for ground truth delineation and provide central study coordination.

### Consent/recruitment

Participants who had their radiation therapy prior to site activation will be recruited retrospectively and a waiver of the need for consent will be sought from an approved HREC (Human Research Ethics Committee) and governing State Health Data Custodian. Participants are otherwise recruited prospectively using a HREC-approved patient information sheet and consent form prior to starting RT.

### Datasets

The minimum RT treatment dataset required from retrospectively recruited participants includes the 3D or 4D CT scans used for planning, contours, treatment plans and pre-treatment 3D or 4D CBCT reconstructed images in DICOM format, and 2D projection images. In-treatment x-ray images are mandatory for prospectively recruited participants and desirable from those retrospectively recruited and any additional images from screening or testing sessions are desirable but not mandatory from all participants.

In addition to RT treatment images, data will be collected on participant characteristics (demographics, medical history, diagnosis), TACE chemotherapy (type of contrast agent - ethiodised oil or drug eluting beads, date of procedure), and other RT treatment-related data (treatment centre and treating doctor, treatment device and version, imaging system type/model, motion management techniques such as free-breathing or breath hold, the use of abdominal compression, and breathing training).

### Matching

Manual delineation of the contrast mass on the planning CT and pre-treatment CBCT images (3D or 4D) with a purpose-designed alignment tool using MATLAB Runtime R2021a (version 9.10) (Fig. 3) will provide a ground truth location of the centre of the contrast mass to which delineation by the KIM software can be compared. If more than one contrast mass is visible on the planning CT and pre-treatment CBCT images, these will be separately delineated, and then the two volumes will be combined into a single contrast mass structure. To ensure at least 100 labelled images will be available for each participant, the contour alignment tool will choose 35 projections per CBCT from each fraction that are equally spaced angularly over the scanning arc to represent a range of angles. Where the contrast agent mass cannot be equivocally identified manually, these images will not be used as the ground truth. Users of the alignment tool will give a confidence score for the alignment using a five-level Likert scale ranging from ‘Not at all confident’ to ‘Very confident’.

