### Comparator

The adapted KIM software will be run on un-delineated copies of the acquired data used to determine the ground truth location of the contrast agent. The KIM program will output the 2D and 3D position of the centre of the contrast agent mass. The KIM algorithm may be adjusted as more patient data is acquired, and the same version of the software will be run across all patients for the analysis.

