### Bias

The study design minimises bias/errors due to sampling (baseline characteristics), matching (accuracy of comparator delineation) and assessments. Baseline characteristics to be considered in final analyses include (i) type, size, shape, density, and location of the contrast agent, (ii) type of imaging and treatment machine, (iii) time since TACE, (iv) participant demographics, and (v) treatment site. Accuracy of the ground truth (manual contrast mass delineation on images) will be maximised by (i) providing sites with the same purpose-designed software to conduct delineation of contrast mass location on images, (ii) for the same projections, performing ground truth delineation by an independent observer who is a member of the research team from another site, and (iii) assessment by qualified and experienced medical physicists or radiation therapists. Final assessment of the KIM software (comparator) will be conducted (i) on images that have not been marked with the ground truth, (ii) by site study personnel who have not seen images marked with ground truth, (iii) by study personnel who are qualified and experienced medical physicists.

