### Outcome measures

(i) the proportion of CBCT projection and intra-treatment images in which the KIM software detects a contrast mass. (ii) the mean and standard deviation of the difference (mm) of location of the centre of the contrast mass detected on CBCT projection and intra-fraction images by KIM software compared with the ground truth in each of the horizontal and vertical directions. (iii) the mean and standard deviation of the centroid error between the segmentation and ground truth will be calculated, and DICE analysis will be performed to measure the similarity between the two delineation methods. Characteristics of the participants, chemotherapy, RT, and images, (e.g., treatment machine type, treatment site; contrast agent type, density, size, shape, and location; and patient size, age, cancer stage and sex), will be used to create a generalised linear model, or appropriate alternative, to identity univariate and multivariate patient or treatment features that contributed to the success or failure of the KIM tracking algorithm.

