## Discussion

The detection of residual radio-opaque contrast in the liver by KIM may lead to the development of technology that improves the accuracy, safety, and effectiveness of RT for liver cancer. The main challenges to this study are the availability of participants whose minimum image dataset is available, especially for retrospectively recruited participants, and the time commitment required by sites to contour images.

The hypotheses will be accepted if, in two thirds of participants (i), KIM detects the contrast mass; (ii) the mean and standard deviation (mm) difference in the location of the mass between ground truth and KIM detection are ≤ 2 mm and ≤ 3 mm, respectively and (iii) if a model of the success rate in the primary hypothesis and patient/treatment characteristics can predict KIM success in 85% of participants. Should the three hypotheses be accepted, there will be sufficient justification for the prospective use of KIM as a real-time image guided radiation therapy tool for liver cancer patients.

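### The scored centre of the merged contrast need not move with the tumour, so passing supports tumour guidance only where the contrast lies in or abuts the SABR target

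*Protocol article*

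**What the plan says.** The Aim section names tumour motion as the quantity of interest: "This study aims to provide a non-invasive alternative to implanting fiducial markers to track tumour movement in real-time during SABR treatment of HCC".

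Four other places in the protocol article determine what is measured.

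- **Eligibility criteria.** Residual contrast must be "from prior TACE chemotherapy visible within the imaging field on RT planning CT scans". No distance to, or overlap with, the SABR target is stated.
- **Matching.** If more than one mass is visible, "these will be separately delineated, and then the two volumes will be combined into a single contrast mass structure". No limit on separation is given, and no mass is singled out as marking the target.
- **Comparator.** "The KIM program will output the 2D and 3D position of the centre of the contrast agent mass".
- **Outcome measures.** Outcome (ii) is the difference in "location of the centre of the contrast mass detected on CBCT projection and intra-fraction images by KIM software compared with the ground truth".

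The acceptance rule in the Discussion sets limits of 2 mm and 3 mm on "the mean and standard deviation (mm) difference in the location of the mass between ground truth and KIM detection". It then treats acceptance of all three hypotheses as enough to justify using the software prospectively for guidance in liver cancer.

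The link between contrast and tumour is given in the Background as common practice: "These retained radio-opaque contrast agents are currently often used as a surrogate tumour marker to aid target verification before and during SABR". The Bias section lists "type, size, shape, density, and location of the contrast agent" among the baseline characteristics to be considered, and the Outcome measures section offers location as a feature for modelling tracking success.

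**The concern.** The decision at the end of the study is about the tumour. The score is about the centre of whatever contrast is visible, merged into one object. As the eligibility sentence is worded, contrast left by chemoembolisation of another lesion would qualify, and two masses in different parts of the liver would be pooled. If such masses move by different amounts, the pooled centre follows neither of them. If the only mass is remote from the target, its centre may not follow the target at all.

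No outcome in the article compares the contrast centre with the position of the tumour or of the planned target. Contrast location enters as a predictor of whether tracking succeeds. That cannot show whether a successfully tracked centre moved with the tumour. At stake is the inference in the Discussion: some participants could count towards justifying prospective guidance although their result says little about tumour position.

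**Working it through.** The plan derives no figure on this point, so there is nothing to reproduce. The check is what a perfect software score implies about the target mass.

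**Inputs.** From the article: the merge rule (Matching), a single scored centre (Comparator, Outcome measures) and the 2 mm limit on the mean (Discussion), used here only as a yardstick. Assumed, because the article gives no values: separation D, motions m_A and m_B, and volume share w, where mass A lies in the target and mass B elsewhere.

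**Formulas.** Merged centre = w × A + (1 − w) × B. Therefore:

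- offset of the merged centre from mass A = (1 − w) × D
- target motion missed when the software finds the merged centre exactly = (1 − w) × (m_A − m_B)
- differential motion that hides a 2 mm miss = 2 / (1 − w)

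**Step 1: static offset.** At D = 40 mm the offset is 0.5 × 40 = 20 mm for equal volumes, 0.3 × 40 = 12 mm for w = 0.7 and 0.1 × 40 = 4 mm for w = 0.9. This alone is not an error in motion tracking: with m_A = m_B the missed motion is 0 whatever D is.

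**Step 2: differential motion.** Take m_A = 15 mm. The scored error is 0 in every cell below.

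| Share of volume in the target mass (w) | Missed motion, m_B = 15 mm | m_B = 10 mm | m_B = 5 mm | Differential motion hiding a 2 mm miss |
|---|---|---|---|---|
| 0.5 | 0 mm | 2.5 mm | 5.0 mm | 2 / 0.5 = 4.0 mm |
| 0.7 | 0 mm | 1.5 mm | 3.0 mm | 2 / 0.3 = 6.7 mm |
| 0.9 | 0 mm | 0.5 mm | 1.0 mm | 2 / 0.1 = 20 mm |

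**Step 3: only a remote mass (w = 0).** The missed motion is the whole of m_A − m_B, so a 2 mm difference gives a 2 mm miss.

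**Limits of the illustration.** The weights are 3D volumes. Outcome (ii) is scored horizontally and vertically on projection images, where separation is foreshortened at many angles and the centre depends on the projected shape. The values above are also per-image displacements, whereas the 2 mm limit applies to a mean. They show the mechanism and its rough scale, and do not predict the study result.

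**The case against.** The strongest reply is that the hypotheses, outcomes and acceptance rule all ask whether the software finds the contrast where a human finds it. The merged structure is the definition of the contrast for both, so the comparison is sound. Testing contrast against tumour position would be a different study. This stands for the comparison itself. It does not cover the Discussion's further step to guidance of liver cancer treatment.

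A second reply is that the Background describes contrast as lying in the tumour and often retained there, so remote contrast may be rare. The full protocol, which is not shown, may also restrict location. Both are possible. They limit how many participants are affected, which is why the point concerns how the results are grouped and read.

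A reader might go further in three ways that the documents do not support.

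- That a centre lying between masses is itself an error. It is not, if masses and tumour move together.
- That the rule wrongly penalises the software for segmenting one mass correctly and missing another. Under the stated definition, missing part of the structure is a genuine segmentation error. With two masses an assumed 40 mm apart and the missed one holding 20% of the volume, the shift is 40 × 0.2 = 8 mm. That is one image under assumed 3D values, and cannot be read as four times a limit on the mean.
- That the scored structure must be replaced. The networks are patient-specific and trained on planning data (Fig. 1 caption), so replacement might mean retraining, and the documents do not show that this is needed.

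**Conclusion.** The point holds as a limit on inference. The article fixes a merge rule and an eligibility rule that do not tie the scored centre to the target, and then draws a conclusion about guidance of tumour treatment. For participants with several masses that move differently, or with contrast remote from the target, that conclusion is unsupported even if the software agrees perfectly with the manual reader.

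The size cannot be stated from the documents. Under the assumed motions, the missed target motion runs from 0 mm (common motion) to 5.0 mm (equal volumes, 10 mm of differential motion). The share of the 50 planned participants affected is unknown and could be small. The verdict rests on the eligibility wording as printed. A location criterion in the full protocol would remove the remote-contrast part. The part about several masses would remain unless that criterion applied to every mass.

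**What to change.** 1. Keep the merged structure as the defined segmentation target.
2. From the separate delineations made under Matching and the planning contours in the minimum dataset (Datasets section), record for each participant the number of masses and the distance from each mass to the target. Add both to the model features under Outcome measures.
3. Report outcomes (i) to (iii) separately for participants with a single mass in or abutting the target and for those with multiple or remote masses. Define abutting before the final analysis.
4. In the Discussion, limit the conclusion on prospective use to the group whose contrast lies in or abuts the target.
5. Where masses can be separated on the projections, add a sensitivity analysis that scores the centroid of the mass in or nearest the target.

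The cost is modest: some extra analysis of contours that are already collected or drawn, with no new imaging or recruitment. The drawbacks are smaller numbers in the group that supports the prospective-use conclusion, and projections that overlap at some angles, so the sensitivity analysis will not be possible on every image.

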**Fig. 3 Fig3:**
[figure not shown]
The contour alignment tool graphical user interface with an unaligned contour. The red contour (liver contrast agent mass) can be repositioned by the user

### Comparator

The adapted KIM software will be run on un-delineated copies of the acquired data used to determine the ground truth location of the contrast agent. The KIM program will output the 2D and 3D position of the centre of the contrast agent mass. The KIM algorithm may be adjusted as more patient data is acquired, and the same version of the software will be run across all patients for the analysis.

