### Preliminary data

To investigate the feasibility of the ROCK-RT protocol, data from three patients recruited into ROCK-RT have been analysed. A conditional generative adversarial network [18] was used to train a patient-specific model to track the contrast mass from the pre-treatment data including data augmentation (translation and rotation). This model was then applied to the data acquired during treatment, representing the clinical scenario of real-time target tracking. Figure 4 shows examples of the target tracking prediction compared with the ground truth. Figure 5 quantifies the centroid error and Dice similarity coefficient acquired from two fractions for three patients using 35 images per fraction. The mean and standard deviation of the centroid tracking error in the anterior-posterior/lateral and super-inferior directions were − 0.4 ± 2.8 mm and − 0.6 ± 1.4 mm respectively. The mean Dice similarity coefficient was 0.87 ± 0.08.

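### The tracking algorithm may be adjusted on study participants and is then scored on all of them, so the acceptance results are liable to be optimistic if adjustment is guided by performance

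*Protocol article*

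**What the plan says.** The Comparator section makes two statements that matter here. On the data: "The adapted KIM software will be run on un-delineated copies of the acquired data used to determine the ground truth location of the contrast agent". On the software, the KIM algorithm "may be adjusted as more patient data is acquired, and the same version of the software will be run across all patients". The Fig. 2 legend gives the same order of work: "After improvement of existing mass-detecting software (KIM) through machine learning, the updated algorithm will be applied to un-delineated images".

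The sample is fixed under Eligibility criteria ("This study will recruit 50 participants who"), with no division into development and test participants. Under Preliminary data, "data from three patients recruited into ROCK-RT have been analysed", to examine the feasibility of the protocol.

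The Discussion sets the decision rule: "The hypotheses will be accepted if, in two thirds of participants (i), KIM detects the contrast mass". It adds the accuracy limits (mean at most 2 mm, SD at most 3 mm) and the 85% prediction criterion. If all three are met, it regards prospective use as sufficiently justified.

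Two safeguards are described. The Fig. 1 legend and Preliminary data say that each network is trained on the patient's own data from before treatment and then applied to treatment images. The Bias section says that the final assessment is made "on images that have not been marked with the ground truth", by staff who have not seen the marked versions.

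**The concern.** A pass/fail threshold says something about future patients only if the scored participants did not help to shape what is scored. Here the algorithm may change as participants accrue, and the version that results is run on everyone, including those who prompted a change. If a change is kept because it improves results on participants already in hand, their results no longer estimate performance in a new patient, on whose treatment images nothing can have been tuned.

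The Bias section's safeguard does not meet this. Unmarked images and unaware assessors control observer bias. They do not make the images new to an algorithm whose design may already have been settled on those same images.

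At stake are the detection proportion, the centroid error and the Dice coefficient. Criterion (iii) models the same success outcome and would inherit any optimism. The margin on accuracy may be thin: the preliminary SD in the anterior-posterior/lateral direction is 2.8 mm against a limit of 3 mm. The SD would have to rise by only 3/2.8 − 1 = 7% to breach it.

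**Working it through.** **Reading the text.** The sample of 50 comes with no stated alpha, power, assumed success rate or precision target, so there is no design figure to reproduce. The point rests on setting the sections side by side:

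- Comparator: adjustment is allowed during accrual, and one version is scored on all patients, on copies of the data that supplied the ground truth.
- Discussion: the criteria are applied to the study's participants, and acceptance supports prospective use.
- Nowhere: a version lock, held-out participants, cross-validation or an external test set.
- Fig. 1 legend and Preliminary data: weights are fitted per patient on pre-treatment data. This closes the most direct route of leakage and leaves the shared design choices.

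**Hypothetical illustration.** Inputs from the article: n = 50 and a two-thirds bar, read at participant level as in the Discussion. The Abstract and Hypotheses place two thirds on images instead, and the illustration does not use that reading. The bar is ceil(50 × 2/3) = ceil(33.3) = 34. Assumptions, not in the article: a true participant success rate of 60%, five candidate versions that are all equally good, and the correlation between versions on a latent normal scale.

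1. One fixed version: P(X ≥ 34) with X ~ Binomial(50, 0.60) = 0.156.
2. Best of five versions, chosen on the number of participants passing (simulation, at least 20,000 runs per row; runs differ by about one point):

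| Correlation between versions | Chance that the best of five reaches 34/50 |
|---|---|
| 0.5 | about 0.46 |
| 0.8 | about 0.38 |
| 0.95 | about 0.30 |
| 0.99 | about 0.24 |

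3. Last of five versions, not chosen on performance: about 0.16 at every correlation, so no inflation.

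At correlation 0.8, the mean apparent success rate of the best of five is 65%, against a true 60%.

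**Cost of a smaller scored set.** The 95% half-width at a proportion of 2/3 is 1.96 × √((2/9)/n):

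- n = 50: 13.1 points
- n = 47 (the three preliminary patients excluded): 13.5 points
- n = 40 (an assumed ten participants excluded): 14.6 points

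With n = 40 the bar is ceil(26.7) = 27, and P(X ≥ 27) with X ~ Binomial(40, 0.60) = 0.211.

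**The case against.** The strongest reply has four parts.

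**Weights are not trained on the scored images.** This stands. A reader might infer that the study reports training-set performance. The article does not support that, because each network is fitted on pre-treatment data and tested on later images. What remains is indirect leakage through shared choices.

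**Adjustment is only permitted, and its trigger is not stated.** This also stands. A change might merely accommodate another imaging system or motion-management technique among those listed under Datasets. A reader might conclude that the results will be optimistic. The text supports only that they are liable to be, if adjustment is guided by performance on these participants. Nor does the article say that the three preliminary patients were used for development: it calls that work feasibility and reports no resulting change.

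**The illustration assumes selection on the endpoint.** True. The article describes no choice among several versions by pass count, the inflation shrinks as versions become more alike, and it vanishes without selection. The figures show a mechanism and do not estimate this study's bias.

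**This is an offline feasibility study, and version control is detail that an article may leave to a fuller document.** In part. The timing of a lock could reasonably be left out. But the article states that one version is scored across all patients, which puts any participant who informed an adjustment into the analysis. Running a common version is sound for consistency; the difficulty is who is included when the criteria are judged.

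**Conclusion.** The concern holds in a conditional form. The article permits adjustment on accruing participants, scores the resulting version on all of them, and lets the result justify prospective use, with no stated protection except blinding of assessors. If adjustment is guided by performance on these participants, detection and accuracy results are liable to favour acceptance.

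The size cannot be derived from the article. Under the hypothetical above, the chance that an algorithm with a true 60% success rate clears the bar rises from 16% to about 24% to 46%. That rests on the participant-level reading of two thirds and on five equally good versions with the best one kept, over correlations from 0.99 to 0.5. If versions are not chosen on performance, it stays at 16%.

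**What to change.** Lock the software version at a stated point before scoring. Keep a record of which participants' treatment images informed any adjustment before the lock, counting the three preliminary patients if their results did. Apply the acceptance criteria to the remaining participants, and report the result for all 50 as secondary. Alternatively, keep all 50 in the primary analysis and use participant-level cross-validation that repeats the whole adjustment process in each fold.

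The first option needs wording and version control, but no new patients or images. It has three costs:

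- Precision falls slightly, from a half-width of 13.1 points to 13.5 (n = 47) or 14.6 (n = 40).
- Chance passes become somewhat more likely in a smaller set: a true 60% algorithm clears 27 of 40 in 21% of trials, against 16% for 34 of 50.
- The criterion (iii) model has fewer participants if it is restricted to the same set.

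Cross-validation avoids the loss of participants, but the adjustment process must be specified well enough to be repeated.
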